## Abstract

**Background:**

The challenge of Bipolar Disorder (BD) treatment is due to the complexity of the disease. Current guidelines represent an effort to help clinicians in their everyday practice but still have limitations, specially concerning to long term treatment. LICAVAL (e*fficacy and tolerability of the combination of **LI**thium and **CA**rbamazepine compared to lithium and **VAL**proic acid in the treatment of young bipolar patients*) study aim to evaluate acute and maintenance phase of BD treatment with two combined drugs.

**Methods:**

LICAVAL is a single site, parallel group, randomized, outcome assessor blinded trial. BD I patients according to the DSM-IV-TR, in depressive, manic,/hypomanic or mixed episode, aged 18 to 35 years are eligible. After the diagnostic assessments, the patients are allocated for one of the groups of treatment (lithium + valproic acid or lithium + carbamazepine). Patients will be followed up for 8 weeks in phase I (acute treatment), 6 months in phase II (continuation treatment) and 12 months in phase III (maintenance treatment). Outcome assessors are blind to the treatment. The main outcome is the evaluation of changes in mean scores on CGI-BP-M between baseline and endpoint at the end of each phase of the study.

**Results:**

LICAVAL is currently in progress, with patients in phase I, II or III. It will extended until august 2012.

**Conclusions:**

Trials comparing specific treatments efficacy in BD (head to head) can show relevant information in clinical practice. Long term treatment is an issue of great important and should be evaluated carefully in more studies as long as BD is a chronic disease.

**Trial registration:**

ClinicalTrials.gov Identifier: NCT00976794

## Background

Bipolar Disorder (BD) treatment is a topic in evolution as long as the understanding of the clinical features, and possible pathophysiology, still progress. Due to multivariate factors associated with its cause and the variability of clinical presentations it's hard to determine a specific treatment with best outcome (efficacy and tolerability). Some difficulties in the BD treatment include: delay in diagnosis, high levels of comorbidity, frequent treatment nonadherence and high risk of relapse/recurrence (mainly in the presence of residual symptoms) [1].

Most treatments focus on acute phase and the measure of response as a reduction in symptoms of at least 50% from baseline. In fact, a number of patients who responded to treatment continue to experience significant subsyndromic symptoms. A small number of studies reported remission rates, which mean at least 2 months with no significant signs or symptoms of the disorder [2]. Fewer studies reported remission during acute phase through maintenance phase of treatment and its predictors [3] what is of great clinical significance. Recent data showed that BD treatment in special conditions was associated with full remission in only half of the patients and that nearly half of the recovered patients relapsed at least once during the two year of follow up [4]. Maintenance treatment is necessary in BD due to its great mortality, morbidity risk and social and professional impairment associated with its poorer outcome [5].

Lithium is first line choice for the maintenance treatment of BD, mainly for classic (euphoric) mania and bipolar depression according to many open controlled studies, with additional clinical effects such as: antisuicidal properties; augmentation and treatment of acute unipolar depression and recurrent depression [6]. The accumulating data tend to support its specificity in psychiatric usage, specially in those patients with "classic" BD. Available clinical trial suggest that better response to valproate are related to dysphoric or mixed episodes and rapid cycling patients [7]. Recently, valproate evidenced benefits on depressive aspects of BD both on acute and prophylactic use [8]. Carbamazepine is associated with better response in: not receiving treatment with mood stabilizers previously; atypical symptoms and signs; dysphoric and rapid cycling patients; treatment resistance to lithium therapy; under 30 years; no family history of BD [7]. Carbamazepine and valproate appear to be effective in the prophylactic treatment of bipolar disorder, especially in combination with lithium, although further studies are desirable [9].

In Brazil lithium is the first treatment choice in all BD phases representing an appropriate treatment of accessible cost. Treatment in the Brazilian Public Health System (*Sistema único de Saúde *- SUS) - have financial limitations once atypical antipsychotics and some anticonvulsants are not available for use in BD. Therefore, the most used treatments for the general population present smaller number of controlled studies in relation to the newest medications in which the pharmaceutical industry has interest in spreading. Although medications such as lithium, valproic acid and carbamazepine have been used for a long time, studies comparing effectiveness and other outcome measures, as well as data of long term combination treatment can still help the adaptation of the public health politics to the patient's real needs (Taveira and Moreno: Survey on treatment of bipolar disorder in Brazil: psychiatrists' epidemiology, prescription drugs and impact on heath policies. Submitted.)

## Methods

### LICAVAL Project

LICAVAL (*efficacy and tolerability of the combination of **LI**thium and **CA**rbamazepine compared to lithium and **VAL**proic acid in the treatment of young bipolar patients*) is a randomized trial designed to evaluate two combined drugs in the treatment of bipolar I patients.

### Design of LICAVAL

The key points of LICAVAL Project come from the rationale described above. We considered the disorder as a whole, that is, different clinical presentations (such as depression, mania or mixed episodes) are receiving the same treatment. The treatment focus is relapse/recurrence prevention and not treating a particular phase. Patients should have a long term follow up as BD is a chronic and recurrent disorder.

This a single site, parallel group, randomized, outcome assessor blinded trial. The study protocol was reviewed and approved by the appropriate institutional review board (Protocol number 0820/08) in accordance with the standards and guidelines established in the current amendment of the Declaration of Helsinki, and consistent with good clinical practice and applicable regulatory requirements. Written informed consent was obtained from all patients prior to any study-related activities. All phases of LICAVAL have their methodological details presented according to Consolidated Standard of Reporting Trials (CONSORT) 2010 Statement [10].

### Interventions

After the diagnostic assessments, the patients are allocated for one of the following groups of treatment:

Group I: lithium + valproic acid

Group II: lithium + carbamazepine

***Lithium***: Starting at 600 mg daily, dose weekly adjusted according to blood serum level (0,6 -1,2mEq/l), efficacy and tolerability

***Valproic acid***: Starting at 500 mg daily, dose weekly adjusted according to blood serum level (50 and 125 μg/ml), efficacy and tolerability

***Carbamazepine***: Starting at 200 mg daily and getting 600 mg daily at the end of the first week. Dose weekly adjusted according to blood serum level (8 and 12 μg/ml), efficacy and tolerability

Concomitant medications are permitted and may continue until remission or symptomatic control needed according to clinical criteria:

•*Lorazepam - 0,5 - 4 mg/day orally*

•*Sertraline - 50 - 200 mg/day orally*

### Eligibility

Patients are recruited in the Institute of Psychiatry, of the Clinical Hospital of the University of Sao Paulo, School of Medicine. BD I patients according to the DSM-IV-TR [2], in depressive, manic,/hypomanic or mixed episode, aged 18 to 35 years are eligible. Patients with psychotic symptoms will be included and will not be stratified. Patients with co-morbid conditions are allowed to participate due to the study clinical reality approach ("more likely naturalistic study").

The patient or his/her legal representative should understand the nature of the study and sign the Informed Consent.

Eligible patients under pharmacological treatments proceed to a wash-out period according to the medication in use: 1 week for antidepressants (except fluoxetine and irreversible MAOI), antipsychotics (except clozapine), lithium, valproate, carbamazepine and other anticonvulsants; 2 weeks for irreversible MAOI; 4 weeks for fluoxetine and clozapine.

### Sample Size and Randomization

Sample size was calculated comparing the mean difference in CGI-BP-M scores between baseline and endpoint for the two groups. If we compare this using a Student's t test we find that with 50 patients (25 in each group) we achieve 80% power (in a 5% of significance level test) to detect a difference of 0.8 standard deviation, which can be considered a large effect size [11]. Due to the exploratory nature of this study and the difficulties of compliance in a long term trial, this seems to be an acceptable value.

The random allocation sequence was computer generated by a biostatistician. Patients were enrolled by clinicians who have their code revealed by the research monitor when assigned to interventions. Blinding the outcome assessor is done keeping their evaluation independent to the clinician.

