### Study phases

Patients will be followed up for 8 weeks in phase I (acute treatment), 6 months in phase II (continuation treatment) and 12 months in phase III (maintenance treatment). Scales raters will be blind to the treatment. During phase II and III will continue only patients that achieve response, measured according to initial symptoms score in phase I. Patients with a new episode of any polarity detected in two consecutives visits will be discontinued from the study.

The definition of clinical course is defined according to Hirschfeld et al (2007) [12], Bauer et al (2007) [13] and Tohen et al (2009) [14]:

Non response: reduction ≤ 25% in severity of symptoms;

Partial response: improvement of symptoms between 26 and 49%;

Response: reduction ≥ 50% in severity of symptoms;

Remission: minimal or no symptoms for at least 1 week;

Sustained remission: at least 8 weeks of remission;

Relapse/recurrence: return of the criteria for the syndrome;

Roughening: return of symptoms in a subsyndromal level.

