### Primary outcomes

Primary outcome will be the evaluation of changes in mean scores on CGI-BP-M between baseline and endpoint at the end of each phase of the study.

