### Planned Analyses

The primary analysis will be the evaluation of the mean scores on CGI-BP-M between baseline and endpoint in both groups. We will also evaluate differences comparing the two groups of treatment concerning total number of patients in full remission at the end of the study and the reason and time to drop out. Continuous data will be represented by mean and standard deviation (SD). Categorical variables will be described by table of frequencies. The results of all statistical comparisons of the treatment groups will be presented as a 2-sided p values rounded to 3 decimal places. The criterion for statistical significance in all comparisons will be p ≤ 0.05.

Continuous variables will be compared using repeated measures analysis of variance (ANOVA), with group of treatment and study phase as factors. Rates of response, remission and drop-outs will be compared between the two groups using a Pearson's X^2 ^test for categorical data. Dichotomous measures will also be compared using odds ratios and 95% confidence limits.

The correlation of clinical issues, quality of life, social adjustment and cognitive impairment will be evaluated by Pearson's correlation.

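### The 80% power is correctly computed for 25 observed patients per group, but it is stated without limit for a primary outcome that is also assessed after two responder-only phases, where it does not apply

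*Protocol article*

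**What the plan says.** All references are to the Methods of the protocol article.

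- **Sample Size and Randomization** bases the size on a Student's t test of the baseline-to-endpoint change in CGI-BP-M. It says that "with 50 patients (25 in each group) we achieve 80% power (in a 5% of significance level test"), and that this is enough "to detect a difference of 0.8 standard deviation, which can be considered a large effect size". It gives no enrolment figure other than 50 and no numerical allowance for loss. The exploratory character of the study and expected compliance problems are offered as reasons to accept the size.
- **Primary outcomes** defines the outcome as the "evaluation of changes in mean scores on CGI-BP-M between baseline and endpoint at the end of each phase of the study".
- **Study phases** sets phase I at 8 weeks, phase II at 6 months and phase III at 12 months. On continuation it says: "During phase II and III will continue only patients that achieve response, measured according to initial symptoms score in phase I". Response means a fall of at least 50% in symptom severity. A patient with a new episode seen at two visits in a row leaves the study.
- **Planned Analyses** has treatment comparisons "presented as a 2-sided p values rounded to 3 decimal places", and compares continuous variables by repeated measures ANOVA with treatment group and study phase as factors.

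**The concern.** The power statement carries no time point, so it reads as covering the primary outcome wherever that outcome is assessed. Two of its three assessment times come after rules that remove non-responders and patients with a new episode. The power figure needs 25 observed patients in each group, and the same document describes a design that thins the groups before those times.

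The later phases are also the ones that bear most on the trial's purpose: Design of LICAVAL places the emphasis on preventing relapse and recurrence. If the maintenance comparison shows no difference, a reader who takes the 80% at face value may conclude that a large difference has been ruled out with good power. The data may not support that.

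**Working it through.** **Inputs from the article.** Significance level 5%, two-sided (Sample Size; Planned Analyses). Standardised difference d = 0.8. n = 25 per group, 1:1. Student's t test.

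**Step 1: reproduce the stated figure.**

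- Normal approximation: n per group = 2(1.960 + 0.842)² / 0.8² = 24.5, rounded up to 25. Power with 25 = Φ(0.8 × √(25/2) − 1.960) = Φ(0.868) = 80.7%.
- Exact t test: noncentrality = d√(n/2) = 0.8 × √12.5 = 2.828, df = 2n − 2 = 48, critical value 2.011. Power = 79.1%.
- A one-sided test would give 87.4%, so the stated 80% is the two-sided figure.

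The calculation is right. It has no slack: the exact t test gives 77.4% with 24 per group.

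**Step 2: apply the article's own continuation rules.** The number observed per group at a later endpoint is 25 × s, where s is the share of randomised patients still in the study. The article gives no response, relapse or dropout rate for this trial, so s is an **assumed range**, equal in both groups, with d held at 0.8. Power is by exact t with noncentrality 0.8√(25s/2) and df = 50s − 2.

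| Share remaining (assumed) | Observed per group | Power for 0.8 SD |
|---|---|---|
| 100% | 25 | 79% |
| 90% | 22.5 | 75% |
| 80% | 20 | 69% |
| 60% | 15 | 56% |
| 50% | 12.5 | 48% |
| 40% | 10 | 39% |

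**Step 3: difference detectable with 80% power.** Solving the same formula for d gives 0.81 SD at 25 per group, 0.91 SD at 20, 1.06 SD at 15 and 1.32 SD at 10 (1.325 before rounding).

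**Step 4: two losses in sequence.** By the end of phase III the share is the proportion responding times the proportion then retained. If both were 80%, s = 0.8 × 0.8 = 0.64, which gives 16 per group and 59% power. If both were 70%, s = 0.49, which gives 12.25 per group and 47%. These proportions are assumptions too.

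**Context only.** The Background cites data in which about half of patients reached full remission and nearly half of those who recovered relapsed over two years. Full remission is stricter than the response needed to continue here, and those were other patients. The data make some loss very likely but do not fix its size.

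**The case against.** **There is no arithmetic error.** This stands. The gap between 79% and 80% is a matter of approximation, and 25 against 26 per group is immaterial. The point concerns the scope of the figure.

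**The article may not be claiming power for phases II and III, and it already hedges.** It calls 0.8 SD a large effect, calls the study exploratory and mentions compliance. This is partly fair, and it lowers the seriousness. But those remarks excuse a large target difference; they do not tell the reader that the 80% stops at the end of phase I. Expected compliance problems would normally lead to an allowance for loss or a qualified claim, and here they lead to neither.

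**Twenty-five per group could still be analysed later.** The article does not say whether 50 means randomised or evaluable patients, or how patients who stop are counted. Carrying scores forward, or another rule that includes everyone, would keep 25 per group in the analysis, and a full protocol or SAP may contain such a rule. So a reader might infer that the design cannot supply 25 per group, and the article does not support a statement that strong. What remains is that carried-forward values are not observations at the end of phase II or III, and that no larger enrolment is given.

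**The powers are for the wrong analysis.** The planned comparison is a repeated measures ANOVA. Its power was not computed, and whether it would be higher or lower is not shown. The SD of change among responders may also differ from that in all randomised patients. Both limits stand: the table extends the article's own sizing method and does not predict the power of the ANOVA.

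**Conclusion.** The point holds as a problem of scope and should be fixed. The stated power is right for 25 observed patients per group, which is attainable at the end of phase I if nobody is lost. It has no margin for loss and does not carry over to the ends of phases II and III, where the article's own rules make fewer than 25 observed patients per group almost certain.

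The size of the shortfall is conditional. By the sizing t test, with 0.8 SD held fixed and equal loss in both groups, power runs from about 75% with 90% remaining to about 39% with 40% remaining. A reader might go further and say that the maintenance comparison has less than 50% power. That needs about half the patients to be gone, and the article gives no figure that establishes it; with 80% to 90% remaining, power is 69% to 75%.

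**What to change.** Change the wording of Sample Size and Randomization:

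1. State that 80% power for 0.8 SD applies to the end of phase I with all 50 patients assessed.
2. State that it does not apply at the ends of phases II and III. Give power or detectable difference there over a retention range that is labelled as assumed, for example 0.91 SD at 20 per group, 1.06 SD at 15 and 1.32 SD at 10. These should be shown as illustrations, so that they are not taken for planned group sizes.
3. Report the later-phase group differences with 95% confidence intervals, and do not interpret a null result there against 80% power.

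No additional patients and no change to the phases or the analysis are needed. The cost is a less favourable stated figure. The rewording does not deal with a separate limitation: a comparison restricted to responders is no longer a comparison of the groups as randomised.

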### Study phases

Patients will be followed up for 8 weeks in phase I (acute treatment), 6 months in phase II (continuation treatment) and 12 months in phase III (maintenance treatment). Scales raters will be blind to the treatment. During phase II and III will continue only patients that achieve response, measured according to initial symptoms score in phase I. Patients with a new episode of any polarity detected in two consecutives visits will be discontinued from the study.

The definition of clinical course is defined according to Hirschfeld et al (2007) [12], Bauer et al (2007) [13] and Tohen et al (2009) [14]:

Non response: reduction ≤ 25% in severity of symptoms;

Partial response: improvement of symptoms between 26 and 49%;

Response: reduction ≥ 50% in severity of symptoms;

Remission: minimal or no symptoms for at least 1 week;

Sustained remission: at least 8 weeks of remission;

Relapse/recurrence: return of the criteria for the syndrome;

Roughening: return of symptoms in a subsyndromal level.

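### The phase II and III CGI-BP-M comparison is made only in patients selected by response and relapse, so it is not a comparison of the groups as randomised, and its bias has no known direction

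*Protocol article*

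**What the plan says.** All references are to the Methods of the protocol article.

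- **Primary outcomes:** the outcome is "changes in mean scores on CGI-BP-M between baseline and endpoint at the end of each phase of the study", so it is required at three time points.
- **Study phases, entry:** "During phase II and III will continue only patients that achieve response, measured according to initial symptoms score in phase I". Response is defined there as a reduction of at least 50% in symptom severity.
- **Study phases, exit:** "Patients with a new episode of any polarity detected in two consecutives visits will be discontinued from the study".
- **Planned Analyses:** "Continuous variables will be compared using repeated measures analysis of variance (ANOVA), with group of treatment and study phase as factors". The sentence on the primary analysis names the CGI-BP-M score from baseline to endpoint in both groups but no model.
- **Sample Size and Randomization:** 25 patients per arm, with which "we achieve 80% power (in a 5% of significance level test"), the target being 0.8 SD between the arms, an effect the section calls large. The calculation is for a t test on the change score. The section mentions compliance difficulties and the exploratory nature of the study, but the number is not raised for either.
- **Design of LICAVAL:** the focus is prevention of relapse and recurrence. No second randomisation is described.

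**The concern.** These statements do not fit together. The primary outcome calls for a score at the end of phases II and III. The phase rules ensure that non-responders never reach those points and that patients who relapse leave before them. These scores are absent by design, which is a different matter from ordinary drop-out.

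Whoever is left has been selected on what happened after randomisation, and the selecting events are closely tied to the outcome. Relapse, the event the trial aims to prevent, removes the patient from the score that is meant to show long-term benefit. Randomisation no longer protects the late contrast or a group effect averaged over phases. A difference there could reflect the drugs or the selection, and so could the absence of one.

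**Working it through.** **1. The plan's own figure.** Inputs from the article: difference 0.8 SD, 5% level, 80% power, 25 per arm. The test is two-sided ("The results of all statistical comparisons of the treatment groups will be presented as a 2-sided p values"; "The criterion for statistical significance in all comparisons will be p ≤ 0.05").

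n per arm = 2 × (1.960 + 0.8416)² / 0.8² = 24.5, rounded up to 25. Power at 25 per arm is 80.7% by the normal approximation and 79.1% by the exact noncentral t. The stated 80% reproduces.

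**2. Who can have a score.**

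| Time point | Patients who can contribute under the phase rules |
|---|---|
| End of phase I (week 8) | all randomised, less ordinary drop-out |
| End of phase II | responders without a discontinuing episode |
| End of phase III | the same, over a further 12 months |

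So 25 per arm can be analysed only at the end of phase I.

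**3. Smaller numbers alone.** The article gives no retention figures, so these are assumptions. The true difference is held at 0.8 SD.

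| Kept per arm | Power (exact t) | Difference detectable with 80% power, 2.8016 × √(2/n) |
|---|---|---|
| 20 (80%) | 69% | 0.89 SD |
| 15 (60%) | 56% | 1.02 SD |
| 10 (40%) | 40% | 1.25 SD |

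**4. Bias from the responder rule.** Assume normal improvement scores with SD 1, response meaning week-8 improvement above a threshold c, and correlation ρ between week-8 and late scores. Let the arms differ by d₁ at week 8 and d₃ later, and let λ(a) = φ(a)/[1 − Φ(a)]. Among responders the expected late difference is

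d₃ − ρ × [λ(c) − λ(c − d₁)].

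Take d₁ = d₃ = 0.8 and 50% response in the worse arm, so c = 0. Then λ(0) = 0.798, λ(−0.8) = 0.368, and the bracket is 0.430. The late difference is 0.671, 0.585 or 0.499 SD for ρ = 0.3, 0.5 or 0.7. Over response rates of 40-60% in the worse arm the range is 0.46-0.69 SD.

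**5. Adding removal of relapsers.** This part was simulated, with relapse taken as a late score more than 0.5 SD below the response threshold. The difference among those still observed falls to 0.36-0.50 SD. With 50% response and ρ = 0.5, 42% and 74% are kept, or 25 × 0.42 = 10.5 against 25 × 0.74 = 18.5 patients. A second set-up used three phases, overall response 50-70%, ρ 0.4-0.6, a relapse threshold 0.25 SD below the response threshold, and 10% and 15% random loss in phases II and III. It gives 0.29-0.40 SD at phase III. Together these are the rough 0.3-0.5 SD.

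The unit is the SD of all patients. In the first set-up selection also reduces the SD to 0.73-0.83, so relative to the remaining spread the difference is about 0.36/0.73 = 0.49 to 0.50/0.83 = 0.60.

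**6. Other true patterns** (50% response in the reference arm, ρ = 0.6).

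| True pattern | Responders only | After relapsers are also removed |
|---|---|---|
| Week 8 −0.5 SD, late 0 | −0.6 × (0.798 − 1.141) = +0.21 | +0.13 |
| Week 8 −0.5 SD, late +0.8 | 0.8 + 0.21 = 1.01 | 0.81 |
| Equal means, SD 1 against 1.5 | 0.6 × 0.798 × 0.5 = +0.24 | +0.44 |
| Week 8 equal, late +0.8 | 0.80 | 0.63 |

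The first and third rows create a late difference that does not exist. The second inflates a real one, though removing relapsers brings it back to about its true size. In the fourth, the responder rule alone does no harm.

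**The case against.** The core is hard to dispute, but several stronger readings are tempting and go too far.

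- **A reader might infer bias toward no difference.** That follows only if one combination is better at every phase. Step 6 shows spurious and inflated differences under other patterns. The direction is unknown; attenuation is plausible.
- **A reader might infer that the week-8 comparison is spoiled too.** This holds only if the ANOVA deletes every patient who lacks a later score. In the second set-up that would cut the week-8 difference to about 0.26-0.37 SD. With 60% response and ρ = 0.6, about 12 and 5.5 patients would remain and power would be some 10-16%, depending on the test. The article states neither deletion of incomplete cases nor an analysis set, and a fuller plan may settle this. Nothing in the phase rules stops all randomised patients being compared at the end of phase I.
- **The ANOVA is not literally named as the primary model.** It is assigned to continuous variables generally. Applying it to CGI-BP-M is the natural reading, and the selection problem affects any comparison of observed late-phase scores.
- **The sizes rest on assumptions.** Response rate, correlation and relapse threshold are not in the article. The calculations use the same score for response and outcome, whereas the Secondary outcomes section links response to HAM-D, MADRS and YMRS as well as CGI-BP-M. A gate on an imperfectly correlated scale would select less strongly.
- **Other analyses keep part of the signal.** Response, remission and drop-out rates, and reason and time to drop out, are also compared. That is real mitigation, but none of these is the primary analysis.
- **The study is called exploratory.** The article uses this to justify a large detectable effect. It does not make the late contrast randomised.

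**Conclusion.** The concern holds for phases II and III and for any group effect pooled over phases. As written, those comparisons are conditional on response and absence of relapse after randomisation. This follows from rules, an outcome and a model that the article itself fixes, so it is not a detail left to an analysis plan.

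The direction of the bias cannot be stated. If one combination is better throughout, 0.8 SD falls to roughly 0.3-0.5 SD under the assumed response rates of 40-70% and correlations of 0.3-0.7. Other patterns produce a false or inflated difference. The 80% power is correct for 25 analysed per arm and does not carry over to the later phases. The end-of-phase-I comparison of all randomised patients stands.

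**What to change.** 1. Make CGI-BP-M change at the end of phase I (week 8), in all randomised patients, the primary score comparison. It is the one time point that matches the sample size calculation.
2. Replace the classical repeated-measures ANOVA by a mixed model for repeated measures on every randomised patient's observed scores, including exit and relapse-visit scores where they are recorded. The article does not say whether they are.
3. Label phase II and III score comparisons among entrants as descriptive.
4. Assess the long-term effect in all randomised patients with non-response, relapse and drop-out counted as outcomes, for example time to treatment failure from randomisation. This fits the stated focus on relapse prevention.

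The continuation and discontinuation rules need not change for any of this. The cost is mainly analysis wording and a different model. The mixed model relies on data being missing at random and extrapolates for non-responders after week 8, who have no later scores at all. If response is judged on other scales, CGI-BP-M alone may not make that assumption reasonable. In simulation the model recovers about 0.8 SD, but only because the simulated data satisfy its assumptions. It does not fully rescue the late-phase score contrast, which is why item 4 is needed.
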